### Data collection and management

#### Plans for assessment and collection of outcomes {18a}

Physiological data will be recorded using the Biopac MP160 recording system (BIOPAC Systems Inc., Goleta, CA, USA) with a sampling rate of 2000 Hz, using the ECG 100C, the GSR 100C, and the RSP 100C amplifiers, and the wirerless Bionomadix transmitters. Three pre-gelled Ag/Ag-Cl ECG electrodes will be placed in lead II ECG configuration. For skin conductance, two self-adhesive Ag/AgACl electrodes prefilled with an isotonic electrolyte medium will be attached to the thenar and hypo-thenar of the non-dominant hand. The BioNomadix respiration transducer will be fastened around either the abdomen or chest depending on the participant’s preferred respiration type. Blood pressure will be acquired with the Dinamap Pro 300 (General Electric Deutschland Holding GmbH, Frankfurt am Main, Germany). A blood pressure cuff will be fastened around the participant’s non-dominant arm. Blood pressure measurement will be automatically triggered via a serial port using a Presentation script.

#### Plans to promote participant retention and complete follow-up {18b}

The duration of the intervention is very short taking approximately 3 h. To increase the likelihood of participation at time point t6 in the evening of testing, a reminder will be sent around via email after the laboratory testing session. Participants may withdraw from the study at any time. The respective data will only be considered if participants finished laboratory testing; otherwise, participants will be excluded from all analyses.

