A VR can target relaxation processes by different mechanisms. In biofeedback, training participants receive online feedback on their physiological responses (e.g., heart rate variability) to learn how to regulate those bodily stress responses [13–16]. Another way VRs can target relaxation processes is by supporting the practice of mindfulness [8, 12, 17]. VRs of this type often use nature scenes combined with nature sounds as a setting [8, 12, 16, 18, 19]. In addition, the feeling of presence generated by the VR could facilitate practicing state awareness, a basic element of mindfulness [8, 12]. In addition, VRs can also serve emotion regulation by distraction which can reduce symptoms of anxiety, depression, fatigue, and pain [20].

Significant effects of VR relaxation interventions have predominantly been found in the domain of self-reported emotional states and less so in physiological measures [16, 19, 21]. VR relaxation interventions led to reduced subjective stress [16], anxiety, and depression [15, 20, 21], as well as reduced negative affect [8, 18, 19], increased state relaxation [8, 21] and relaxation self-efficacy [13], increased recreation [19], and enhanced positive affect [12, 19].

In the current randomized controlled non-inferiority trial, we will test a newly developed VR for relaxation against an active control group applying a freely chosen relaxation method. We hypothesize non-inferiority of the VR, assuming that the VR is equally effective as a freely chosen, preferred, and well-practiced relaxation method. So far, the majority of studies evaluated the respective relaxation intervention in a calm and comforting setting. This raises the question, if participants will be capable to use the respective relaxation intervention also in stressful situations, when the intervention would be most needed and processing resources are limited. We therefore implement the VR not only for relaxation but to downregulate stress induced before the relaxation phase.

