### Assignment of interventions: blinding

#### Who will be blinded {17a}

Since participants will be blinded until the onset of the relaxation phase, baseline and stress phases will not be influenced by group assignment. Blinding participants for the relaxation phase will not be possible since either the VR or an own relaxation method will be applied. Similarly, blinding is not possible for the experimenters. The data analysis will comprise two separate processing stages: analysis of raw data in Matlab 2020b (The Mathworks Inc., Natick, MA, USA) and statistical tests in SPSS Statistics 27 (Armonk, NY: IBM Corp.). Missing values and outliers will be treated at the first analysis stage. The data analyst will be blinded until the performance of the statistical test at the second analysis stage.

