#### Procedure for unblinding if needed {17b}

Participants will be unblinded immediately before the relaxation phase by revealing their allocation and giving the respective instructions. The data analyst will be unblinded at the second analysis stage.

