#### Methods in analysis to handle protocol non-adherence and any statistical methods to handle missing data {20c}

Missing values will be replaced by multiple imputation; missing segments in the physiological data will be discarded.

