#### Adverse event reporting and harms {22}

We do not expect any serious adverse events or adverse events from the relaxation interventions. The stress induction paradigm has been applied to more than two hundred healthy participants of the same age range at different study sites without the occurrence of any serious adverse events [30, 42, 43]. The only minor adverse event that we observed in former studies is the experienced psychological distress causing approximately 3% of study participants to withdraw from the study. The trial management group will document any adverse events and report it to the lead investigator. Unexpected, serious, and severe events occurring during the trial will be reported to the local ethics committee that approved the study. An intern physician can always be contacted concerning health-related questions.

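### Excluding everyone who does not finish the laboratory session, including those who leave knowing their arm, can bias the non-inferiority comparison in either direction

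*Protocol article*

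**What the plan says.** All references are to the protocol article.

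- **Analysis set, {18b}.** On participants who withdraw: "The respective data will only be considered if participants finished laboratory testing; otherwise, participants will be excluded from all analyses". No section names an analysis of all randomised participants.
- **Missing data, {20c}.** "Missing values will be replaced by multiple imputation; missing segments in the physiological data will be discarded". The imputation model is not described.
- **Timing of the reveal, {17b}.** "Participants will be unblinded immediately before the relaxation phase by revealing their allocation and giving the respective instructions". The blinding section {17a} adds: "Since participants will be blinded until the onset of the relaxation phase, baseline and stress phases will not be influenced by group assignment".
- **Blinding of the analyst, {17a}.** "Missing values and outliers will be treated at the first analysis stage", and "The data analyst will be blinded until the performance of the statistical test at the second analysis stage".
- **Withdrawal rate, {22}.** The only rate given comes from former studies: "experienced psychological distress causing approximately 3% of study participants to withdraw from the study".
- **Hypothesis, {6a}.** "We hypothesize non-inferiority of the VR, assuming that the VR is equally effective as a freely chosen, preferred, and well-practiced relaxation method".

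**The concern.** The rule conditions the analysis on something that happens after randomisation and, for part of the session, after the participant knows and is experiencing the assigned arm. The arms differ in what might make someone leave. One has a headset, massage, heat and paced breathing with breath-holds; the other has an activity the participant chose. A person who leaves because the VR did not help or was unpleasant is a poor VR result, and the rule deletes that result.

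Two consequences follow from the text itself.

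- Ratings are taken after relaxation and again around a later recovery phase. Someone who leaves during recovery has already supplied the post-relaxation rating that the group t tests in {20a} need, and that observed value is discarded.
- Imputation is planned, but it can serve only finishers. It cannot reach the participants whose missing values are most likely to be informative.

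In a non-inferiority trial, a loss of poor results confined to the new arm makes a false claim easier, and the plan has no second analysis set that would show it.

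**Working it through.** **Inputs from the protocol.** Sample size {14}: 80% success in both groups, margin 25 percentage points, alpha 0.05, power 90%, total 88, raised to 100 for dropouts. Trial design {8}: 1:1 allocation. Interim analyses {21b}: at least 50 per group.

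**Reproducing the plan's figure.** n per arm = (z_alpha + z_power)² × [0.8 × 0.2 + 0.8 × 0.2] / 0.25².

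- One-sided 0.05: (1.645 + 1.282)² × 0.32 / 0.0625 = 43.8, so 44 per arm and 88 in total. This matches.
- One-sided 0.025: 53.8, so 54 per arm and 108 in total. This does not match.

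The check therefore uses one-sided 0.05. Raising 88 to 100 leaves room for 12% losses (1 − 88/100).

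**Assumptions.** The success scale of {14} is used because it is the only one with a stated margin, although the primary outcomes are 0 to 9 ratings. The true difference sits at the margin: control 0.80, VR 0.55, 50 per arm. Leavers make up a share d of an arm and all count as failures. The values d = 3, 6 and 12% are assumed; 12% is the whole dropout allowance.

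**Formula.** Among completers, an arm that loses a share d of failures has success p/(1 − d) on 50(1 − d) participants. With SE = √[p_C(1 − p_C)/n_C + p_V(1 − p_V)/n_V], the chance of declaring non-inferiority is Φ[(p_V − p_C + 0.25)/SE − 1.645].

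**Worked case, VR-only loss of 12%.** p_V = 0.55/0.88 = 0.625 and n_V = 44. The apparent difference is 0.625 − 0.80 = −0.175. SE = √(0.16/50 + 0.2344/44) = 0.0923. (−0.175 + 0.25)/0.0923 = 0.812, and Φ(0.812 − 1.645) = 20.3%.

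| Who leaves | d = 3% | d = 6% | d = 12% |
|---|---|---|---|
| VR failures only | 7.2% | 10.4% | 20.3% |
| Failures, same share in both arms | 4.2% | 3.4% | 2.0% |
| Control failures only | 2.7% | 1.3% | 0.2% |
| Unrelated to arm and response | 5.0% | 5.0% | 5.0% |

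With nobody excluded the rate is 5.0%.

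**Imputation, conditional check.** This simulation used 6,000 runs, 10 imputations, Rubin's rules and values missing completely at random, with the same true difference of −0.25. If group were left out of the model, assumed missing shares of 5, 10 and 20% give mean estimates of −0.236, −0.224 and −0.199 and error rates of about 6.3, 6.8 and 8.1%. With group in the model the error stays at 4.8 to 5.6%.

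**The case against.** **Most expected withdrawals may be harmless.** The one stated rate, about 3%, is attributed to distress in former studies with the stress paradigm. Here that task precedes the reveal, so such losses mainly cost power. The adverse-event section also expects no adverse events from the relaxation interventions. This stands: nothing in the documents shows that losses after the reveal will be common.

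**Leaving the session is not the same as stopping the intervention.** A participant who takes off the headset but stays for the ratings has finished testing and, on the text, is kept. Adherence is measured in {11c}, and nobody is excluded for it. This also stands. The point covers only those who leave the session.

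**The direction is not fixed.** A reader might infer that the rule pushes the result towards non-inferiority. The table does not support that: only the first row exceeds 5%.

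**Blinded imputation is not imputation without group.** A reader might also infer from {17a} that the imputation pools the arms and so shrinks the difference. The documents never say that group is omitted, and a masked code is compatible with a blinded analyst. The model is a detail that an analysis plan may hold. Because non-finishers are already removed and laboratory ratings are logged electronically, gaps among finishers should fall mainly on the evening rating, for which {18b} plans a reminder. Any effect on the post-relaxation comparison is probably small.

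None of this answers the rule itself. It is stated outright, covers all analyses, and removes observed post-relaxation data.

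**Conclusion.** The point holds in this limited form: {18b} fixes a completers-only set that can remove participants who leave knowing their arm, together with ratings they have already given, and no analysis of a fuller set accompanies it. The resulting bias can go either way.

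Under the adverse scenario, with VR failures alone leaving, the one-sided error is about 7 to 20% instead of 5%. Under the other scenarios it is 5% or lower. These figures rest on the assumed loss shares, on counting every leaver as a failure, and on a success scale that is not the scale of the primary outcomes. They show what the rule permits and do not forecast what happened. Analysis in the assigned arm is not abandoned, since nobody is moved between arms; what is lost is the full set of participants randomised and told their arm. The imputation question is a risk to close off, not an error in the plan.

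**What to change.** 1. In {18b}, define the main analysis set as all participants whose allocation was revealed, analysed in the arm assigned. Use every rating they gave, and the multiple imputation already planned in {20c} for the rest. Leaving out those who withdraw before the reveal relies on the participant blinding described in {17a}.
2. Keep the completers as a second analysis. Whether a claim should require both sets to agree is a matter of convention; state the choice in advance.
3. Add a sensitivity analysis that gives VR non-finishers unfavourable values.
4. Report the number of stops by arm and by phase, so that readers can see which row of the table is closest.
5. As a safeguard, state in {20c} and {17a} that the imputation model includes a masked A/B group code, so that the blinded first stage does not pool the arms.

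The cost is a change of wording in three sections, a little more analysis work and a slightly wider interval. No additional data collection is needed.

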#### Data management {19}

All physiological data recorded with the Biopac MP160 recording system as well as ratings and questionnaires assessed with the software Presentation and the online survey tool limesurvey are electronically logged. The only information that will be acquired in paper form and that will be entered manually is the protocol sheet with the blood pressure measurements and two additional questionnaires. One research assistant from the recruiters will enter them, another one will control for errors in data entry. Participants’ written consent forms will be stored for 10 years in numerical order in a locked cabinet.

#### Confidentiality {27}

Collected data will be identified by a coded ID number to maintain participant confidentiality. All records that contain names or other personal identifiers, such as informed consent forms, will be stored separately from study records identified by code number

#### Plans for collection, laboratory evaluation, and storage of biological specimens for genetic or molecular analysis in this trial/future use {33}

No biological specimens will be collected.

### Statistical methods

#### Statistical methods for primary and secondary outcomes {20a}

Analysis of acquired raw data will be conducted in Matlab 2020b (the Mathworks Inc., Natick, MA, USA). All physiological data will be visually screened. ECG data will be analyzed with the Pan-Tompkins algorithm for QRS detection [38, 39]. Heart rate will be estimated as the number of beats per minute. Heart rate variability will be estimated using root mean square of successive differences (RMSSD, [40]). The tonic skin conductance level and the number of non-specific phasic skin conductance responses will be estimated using the matlab toolbox Ledalab [41]. Respiratory rate will be estimated per minute using a custom-made matlab script that band pass filters the data to frequencies of 0.05 to 1 Hz before detection of inhalation peaks and exhalation troughs. SPSS Statistics 27 for Windows (Armonk, NY: IBM Corp.) will be used for statistical analyses. To test the effects of time (within-subject factor), group (between-subject factor), and the time by group interaction, repeated measures ANOVAs will be performed. Additional two sample *t* tests will evaluate the group differences at relaxation and post-relaxation.

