**Methods:**

One hundred healthy participants will be recruited from the University of Siegen and randomly assigned to the VR or the active control group that will be free to choose their own relaxation strategy. The multi-sensory VR includes visual, acoustic, and haptic features to induce a strong feeling of presence. The laboratory testing will comprise a baseline measurement, a stress induction, a relaxation intervention, and a recovery measurement. The primary outcomes are self-reported stress and relaxation measured with a visual analog scale (VAS) at pre- and post-baseline, at the start, middle, and end of the stress induction, at pre- and post-relaxation, at pre- and post-recovery, and in the evening of testing. Secondary outcomes are the physiological parameters, namely heart rate and heart rate variability, tonic skin conductance level as well as the number of non-specific skin conductance responses, systolic and diastolic blood pressure and respiratory rate recorded during the four experimental phases as well as state mood, and state rumination assessed at four time points (pre- and post-stress, post-relaxation, and in the evening of testing). Finally, post-event processing will be assessed after relaxation and in the evening of testing. Repeated measures ANOVAs will be performed to test for statistical effects of group, time, and group × time interaction.

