### Objectives {7}

Our main objective is to investigate if the VR intervention is non-inferior to an active control group, applying a freely chosen relaxation method, in inducing stress reduction and relaxation indicated by ratings and physiological measures.

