### Outcomes {12}

The primary outcomes are self-reported stress and relaxation measured with a visual analog scale (VAS) at pre- and post-baseline (t2); at the start, middle, and end of the stress induction (t3); at pre- and post-relaxation (t4); at pre- and post-recovery (t5); and in the evening of testing (t6). Secondary outcomes are the physiological parameters, namely heart rate and heart rate variability, tonic skin conductance level as well as the number of non-specific skin conductance responses, systolic and diastolic blood pressure and respiratory rate recorded during the four experimental phases at time points t2 to t5 as well as state mood, and state rumination assessed at four time points (at t2 baseline/pre-stress, at t3 post-stress, at t4 post-relaxation, and at t6 in the evening of testing). Finally, post-event processing will be assessed at t5 after relaxation and at t6 in the evening of testing

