### Sample size {14}

Apriori power analyses were performed for a non-inferiority trial in Sealed Envelope Ltd. 2012 [37]. To achieve a power of 90% at an alpha level of 0.05 assuming a non-inferiority margin of 25% and 80% success in both groups, the estimated required sample size is 88. Considering potential dropouts, we decided to acquire data from 100 participants

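### The trial is framed and sized for non-inferiority, but the stated analyses test only for a difference and never use the margin

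*Protocol article*

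**What the plan says.** The aim is stated in Objectives {7}: "Our main objective is to investigate if the VR intervention is non-inferior to an active control group". Background and rationale {6a} gives the hypothesis: "We hypothesize non-inferiority of the VR, assuming that the VR is equally effective as a freely chosen, preferred, and well-practiced relaxation method". Sample size {14} is a non-inferiority calculation, introduced with "To achieve a power of 90% at an alpha level of 0.05"; it assumes a 25% margin and 80% success in both groups, arrives at 88, and is raised to 100 for dropout.

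The primary outcomes in {12} are stress and relaxation ratings, which the procedure in {11a} scores from 0 to 9. For these and the secondary outcomes, {20a} says: "To test the effects of time (within-subject factor), group (between-subject factor), and the time by group interaction, repeated measures ANOVAs will be performed". It then adds: "Additional two sample *t* tests will evaluate the group differences at relaxation and post-relaxation". The abstract repeats the ANOVA plan: "Repeated measures ANOVAs will be performed to test for statistical effects of group, time, and group × time interaction". Interim analyses {21b} refers back to {20a} as the place where the planned analyses are described, and {20b} only adds covariates to the same models.

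**The concern.** The F tests for group and for group by time, and the t tests as described, take no difference as the null hypothesis. Failing to reject that null does not show that VR is no worse than control by more than a tolerated amount. Rejecting it does not show that VR is worse by more than that amount. A non-inferiority conclusion needs a margin and a confidence limit, or a shifted null, to set against it. The margin appears only in {14}, and nothing in {20a} connects to it.

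At stake is the trial's main conclusion. If a non-significant result were taken as support, the chance of calling a materially worse VR non-inferior would not be held at the 5% assumed in the sample size. It would also grow as the sample shrinks or the ratings become noisier.

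**Working it through.** **1. Reproduce the plan's figure.** Inputs from {14}: success 0.80 in both arms, margin 0.25, power 90%, alpha 0.05 (sidedness not stated).

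n per arm = (z₁₋α + z₀.₉₀)² × [0.80×0.20 + 0.80×0.20] / 0.25²

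- One-sided 0.05: (1.645 + 1.282)² × 0.32 / 0.0625 = 43.8, so 44 per arm and **88** in total. This matches.
- One-sided 0.025: 54 per arm, 108 in total. No match.
- A test of difference, 80% against 55%, 90% power, without continuity correction: 144 in total two-sided, 118 one-sided. No match.

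The 88 is therefore arithmetically right, but it belongs to a one-sided 5% margin test of two proportions that {20a} does not contain.

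**2. Error at the margin, on the plan's own scale.** Let VR be worse by exactly the margin: 0.55 against 0.80. Take a two-sided 5% difference test (an assumption, since {20a} states neither level nor sidedness). At 50 per arm the pooled proportion is 0.675.

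- SE under the null = √(2 × 0.675 × 0.325 / 50) = 0.0937
- SE under the alternative = √((0.16 + 0.2475) / 50) = 0.0903
- P(significant) = Φ((0.25 − 1.96 × 0.0937) / 0.0903) = Φ(0.74) ≈ 0.77, so P(non-significant) ≈ 0.23

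Exact binomial enumeration at the same truth:

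| Per arm | Difference test non-significant | Margin-based bound wrongly declares non-inferiority |
|---|---|---|
| 50 | 22.8% | 4.8% |
| 44 | 26.9% | 4.6% |
| 25 | 50.7% | 4.9% |

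The last row is the N = 50 look in {21b}, if it splits evenly.

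**3. Error at the margin, on the rating scale.** The article gives no margin and no SD for the ratings, so both are assumptions shown as a range. For a two-sided 5% t test with n per arm and a true deficit of d SD, the statistic is non-central t with 2n − 2 degrees of freedom and non-centrality d√(n/2). For d = 0.5 and n = 50 the non-centrality is 2.5 and the critical value 1.984. Probability of a non-significant result when the deficit equals the margin:

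| Assumed margin (SD) | 0.3 | 0.4 | 0.5 | 0.6 | 0.72 |
|---|---|---|---|---|---|
| 50 per arm | 68.2% | 49.2% | 30.3% | 15.6% | 5.7% |
| 44 per arm | 71.5% | 54.2% | 36.0% | 20.5% | 8.7% |
| 25 per arm | 82.0% | 71.7% | 59.0% | 45.3% | 30.1% |

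The 0.72 SD column is what 80% against 55% would mean if success were a cut-off on a normal rating: z₀.₈₀ − z₀.₅₅ = 0.842 − 0.126 = 0.716.

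**4. Power of a margin-based analysis.** With no true difference and one-sided 5%:

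- Success proportions, 25-point margin: 90.1% at 44 per arm, 93.1% at 50.
- Ratings, 50 per arm: 44% for a margin of 0.3 SD, 63% for 0.4, 80% for 0.5. For 90% the margin must be about (1.645 + 1.282) × √(2/50) ≈ 0.59 SD.

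**The case against.** A reader might infer that the investigators intend to treat non-significance as proof of non-inferiority. No section says so. The wording in {6a} that VR is equally effective, together with the absence of any other decision rule, makes that reading possible, but it remains a risk and not a stated plan.

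A two-sample t test also yields a confidence interval for the difference, which is the usual vehicle for a margin comparison. The planned tools could therefore serve. What is missing is the margin on the analysed scale and the rule, not the software or the data.

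A reader might also take 68% or 30% as the plan's error rate. Those figures hold only if the margin is 0.3 or 0.5 SD. If it were 0.72 SD, such deficits would lie inside it, declaring non-inferiority would be correct, and the error at the margin with 50 per arm would be about 6%, close to nominal. The 23% in turn applies to an analysis of success proportions, not to a t test on ratings.

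Finally, this is a condensed article: {31c} cites a posted protocol version, and an analysis plan may exist. Interval levels could be left to those documents. That does not remove the mismatch, because {20a} does not leave the analysis open: it names the tests, the abstract repeats the ANOVAs, and {21b} treats {20a} as the plan.

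**Conclusion.** The point holds in this form: the objective, hypothesis and sample size are non-inferiority, the stated tests are tests of difference, and the margin is used only to obtain N. Followed as written, the plan does not test its main objective.

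The size depends on the scale. On the plan's own success figures, reading non-significance as non-inferiority would err in about 23% of trials at 50 per arm and 27% at 44 when VR is worse by the full margin, against about 5% for a margin-based bound. On the ratings the answer runs from 68% to 6% at 50 per arm, depending on a margin and SD that are not given. These figures assume a two-sided 5% test and, for the ratings, normality with equal variances. The sample size itself is not an arithmetic error. Because the defect concerns the primary conclusion, it should be corrected before the group results are analysed.

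**What to change.** In {20a}, make the primary analysis one of the following:

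- the VR minus control difference at the post-relaxation rating, with a one-sided 95% confidence limit (equivalently a two-sided 90% interval, matching the alpha behind N = 88), compared with a justified margin in rating points: the upper limit for stress, the lower limit for relaxation; or
- a defined success on the ratings, analysed against the 25-point margin.

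State whether both stress and relaxation must meet the margin. Keep the ANOVAs as supportive analyses, and say that their non-significance is not evidence of non-inferiority.

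The cost is mainly one of timing and power. The interval comes from the same data and software. However, Trial status reports that recruitment ended in May 2021, and {21b} has the lead investigator analyse data at N = 50. The margin or success definition should therefore be set and dated before the group results are examined, by someone who has not seen them. Power on the rating scale depends on the margin chosen (44% at 0.3 SD to 90% at about 0.59 SD with 50 per arm). The stated 90% therefore applies only to the success-proportion analysis unless power is restated.

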#### Methods for additional analyses (e.g., subgroup analyses) {20b}

To explore if the current stress level, trait mindfulness, and trait self-efficacy impact the success of the applied relaxation method, we will include them as covariates in the above models. No additional subgroup or adjusted analyses are planned.

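### The post-relaxation group comparison is an unadjusted t test, although same-scale ratings taken before allocation is revealed are available; ANCOVA on them would probably be more precise at negligible cost

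*Protocol article*

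**What the plan says.** - **Analysis.** Section {20a} plans repeated measures ANOVAs with time, group and their interaction. It then adds two-sample t "tests will evaluate the group differences at relaxation and post-relaxation". No covariate is named for either.
- **Adjustment.** Section {20b} enters three covariates into these models in order to explore their influence: a current stress level that is not defined, trait mindfulness and trait self-efficacy. It ends: "No additional subgroup or adjusted analyses are planned".
- **Available earlier values.** Under Outcomes {12}, stress and relaxation are rated at ten points. Two are at baseline, three during the stress induction, and one each before and after relaxation. Heart rate, heart rate variability, skin conductance, blood pressure, respiration, mood and rumination also have t2 and t3 values.
- **Timing of disclosure.** Sections {17a} and {17b} keep participants blinded through the baseline and stress phases and reveal allocation immediately before relaxation.
- **Sample size.** Section {14} works on a binary scale, "assuming a non-inferiority margin of 25% and 80% success in both groups", and concludes that "the estimated required sample size is 88". The target is 100, or 50 per group.

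**The concern.** A participant's level after 15 minutes of relaxation is likely to depend partly on how stressed that person was when relaxation began. A t test on the post-relaxation value alone leaves all of that between-person variation in the error term. Randomization is simple and unstratified ({16a}), so the design does not balance stress response either.

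The needed covariate is already recorded, on the same scale, before anyone knows their group. The trial's question is whether the VR is non-inferior, and such a question is settled by where a confidence bound falls, so precision at this time point matters. The unadjusted comparison is stated, and further adjusted analyses are expressly excluded. This is therefore a choice the article makes, and not a detail left to a later analysis plan.

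**Working it through.** **1. Reproduce the stated sample size.** Inputs from {14}: success 0.80 in both groups, margin 0.25, power 90%, alpha 0.05 (sidedness not stated). With one-sided alpha:

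n per group = (1.645 + 1.282)² × 2 × 0.8 × 0.2 / 0.25² = 8.56 × 0.32 / 0.0625 ≈ 43.9, so 44 per group and 88 in total.

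This matches. One-sided 0.025 gives 54 per group (108) and does not. A one-sided 5% bound, which is one end of a two-sided 90% interval, is therefore used below.

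**2. Interval from the planned t test,** in SD units of the post-relaxation rating, with m = 50 per group and N = 100:

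half-width = t(0.95; 98) × √(2/50) = 1.661 × 0.200 = 0.332 SD.

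**3. Interval from ANCOVA with one pre-disclosure covariate:**

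half-width = t(0.95; 97) × √[(2/50)(1 − r²)(1 + 1/96)].

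The correlation r between the t3 and post-relaxation values is not in the article. It is an assumption, shown over a range. Effective N is 100/(1 − r²). The last column is a change score from t3, assuming equal SDs, with half-width t(0.95; 98) × √[(2/50) × 2(1 − r)].

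| Assumed r | ANCOVA half-width (SD) | Ratio to t test | Effective N | Change-score ratio to t test |
|---|---|---|---|---|
| 0 | 0.334 | 1.005 | 100 | 1.41 |
| 0.1 | 0.332 | 1.000 | 101 | 1.34 |
| 0.3 | 0.319 | 0.96 | 110 | 1.18 |
| 0.5 | 0.289 | 0.87 | 133 | 1.00 |
| 0.7 | 0.238 | 0.72 | 196 | 0.78 |

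Break-even for ANCOVA against the t test is r ≈ 0.10. With 88 participants, the half-width is 0.355 SD unadjusted, against 0.340, 0.309 and 0.255 at r = 0.3, 0.5 and 0.7.

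**4. Check by simulation.** For 4,000 simulated trials of 100, the ratios were 0.959, 0.871 and 0.719 at r = 0.3, 0.5 and 0.7. Coverage of the 90% interval was 90.6%, 90.3% and 90.0%.

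**5. Cost of a second covariate.** If t2 is added, r becomes the multiple correlation and the inflation term becomes 1 + 2/95. If neither covariate predicts anything, the interval widens by a factor of √(1 + 2/95) ≈ 1.01, or about 1%.

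**The case against.** **The ANOVA is the main analysis and already uses the earlier ratings.** This stands in part. The t tests are labelled additional, and the group-by-time term does compare change between groups. But that term is an omnibus test over several occasions and gives no single post-relaxation difference with an interval. If all ten ratings enter, the five from baseline and stress precede disclosure, so they can only dilute the group main effect. Even a single contrast from t3 to post-relaxation is a change score, and the table shows it is less precise than ANCOVA at every r listed.

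**Adjustment is not wholly absent.** True. Section {20b} plans covariate models, and its current stress level could mean the state rating. It more likely means the perceived stress questionnaire, which the Procedure lists with the self-efficacy and mindfulness scales. Either way the use is exploratory and does not set the main comparison.

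**The gain is not guaranteed.** True. It rests on an r the article does not give, and a bounded 0 to 9 scale after a strong stressor could make r modest.

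**A reader might infer that the t test is biased by chance imbalance in stress response.** It is not. Under randomization the unadjusted difference is unbiased, and chance imbalance is already in its standard error. At r = 0.5, a one-standard-error imbalance (0.20 SD) shifts the raw difference by 0.10 SD. Its variance, 0.01, is 25% of the total 0.04. That is the same 1 − r² gain, not a second benefit.

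**A reader might also infer that the plan's non-inferiority interval is too wide.** The article contains no such interval. Its only margin is 25 percentage points on a success that it does not define, and {20a} gives no margin on the rating scale.

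**Conclusion.** The point holds as one of efficiency. The only direct comparison at relaxation and post-relaxation leaves unused a same-scale value recorded before disclosure, and {20b} excludes further adjusted analyses. Using that value would narrow the 90% interval by about 4%, 13% or 28% at assumed r = 0.3, 0.5 or 0.7, with 50 per group. At worst it would widen it by about 0.5% with one covariate or 1% with two. These figures assume a linear relation with the same slope in both groups.

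The planned t test remains valid, and nothing here shows the trial to be underpowered: the 88 reproduces on its own binary assumptions. Nor does adjustment remedy the missing link between the binary margin and the rating scale. That is a separate problem, and any bound eventually compared with a rating-scale margin would benefit from this change only once such a margin exists.

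**What to change.** - Replace the post-relaxation t tests with ANCOVA: post-relaxation value on group, with the t3 (and t2) value of the same measure as covariates. Do the same for secondary outcomes that have t2 and t3 values, namely physiology, mood and rumination. Post-event processing has no earlier value.
- Do not use the pre-relaxation rating as a covariate unless it is confirmed to be recorded before allocation is disclosed. The article does not settle the order.
- Report the adjusted group difference with its confidence interval, and take any non-inferiority bound from this model.
- Amend the last sentence of {20b} to match, and define the current stress level named there.

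The cost is one model statement, no new data and one or two degrees of freedom. Timing needs care: recruitment ended in May 2021, and {21b} has the lead investigator analyse the data at N = 50. The change should be a dated amendment made before the group comparisons are seen, stating whether interim group results were already known.
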